#### 6. Method of participant selection

##### 6-1. Eligible patient and method of recruitment

Those who undergo surgery under intraoperative management by total intravenous anesthesia in the Department of Neurosurgery or Plastic Surgery at Kurume University Hospital

The target number of cases: 20 patients

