### 8-1. Detailed procedure

The patient will be brought into the operation room with usual medical procedure, and a commercially available BIS sensor will be attached to the forehead of the patients immediately after the introduction of anesthesia needle electrodes, and the perioperative consciousness levels and association in various BIS-related values will be compared.

- I. Before the introduction of anesthesia, both needle electrodes and a commercially available BIS sensor will be attached at the same place of the forehead
- II. Anesthesia will be introduced by propofol, remifentanyl, and rocuronium
- III. Normal anesthesia management will be done
- IV. Because the needle electrodes and the commercially available BIS sensor are at the same position, there should be no difference. The BIS monitoring system used in this study can display BIS

values from two areas, and the electrodes are attached at the same position. The homology of the EEG wave form will be observed, values calculated using EEG processing, such as SQL, SEF, Beta-ratio, and resting ratio, will be compared and recorded if there is any discrepancy and if so in which degree.

- V. After completion of the surgery, it will be recorded if there is any discrepancy and if so in which degree in increasing BIS values due to emergence.

8-2. Devices to be used (All of them are medical devices approved for clinical use)

1. NE-220B, the needle electrodes for EEG manufactured by Nihon Koden (length, 13mm; diameter 0.4mm).
2. BIS™ Complete 4 Channel Monitoring System
3. BIS™ Bilateral Sensor

8-3. Methods of allocation

This study acquires and compares information from two sensor locations in a single person. Therefore, there is no allocation.

8-4. Endpoints

Primary endpoints : BIS-related values from two different measurement locations

Secondary endpoints: perioperative complications

8-5. Analysis methods

By repeated ANOVA (post hoc test) and sequential two-group comparisons of BIS-related values, it will be proven that the observed values are the same.

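### Section 8-3 dispenses with allocation because each patient is their own control, but pairing does not remove a position or monitor-input offset, and the protocol describes electrode placement in two incompatible ways

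*Protocol*

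**What the plan says.** The protocol describes the placement of the two electrode sets in several places.

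- Section 8-1, step I: "both needle electrodes and a commercially available BIS sensor will be attached at the same place of the forehead".
- Section 8-1, step IV: "Because the needle electrodes and the commercially available BIS sensor are at the same position, there should be no difference". The next sentence says that the monitor can show BIS "values from two areas, and the electrodes are attached at the same position".
- Section 8-3: "This study acquires and compares information from two sensor locations in a single person. Therefore, there is no allocation".
- Section 8-4, primary endpoint: "BIS-related values from two different measurement locations".

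Section 8-2 lists one monitor, the "BIS™ Complete 4 Channel Monitoring System", and a bilateral sensor. Section 8-5 gives the analysis: "By repeated ANOVA (post hoc test) and sequential two-group comparisons of BIS-related values, it will be proven that the observed values are the same". Section 6-1 sets the size: "The target number of cases: 20 patients".

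No section says which side, relative position or monitor input carries the needle set, whether this is the same in every patient, or that it is to be written down.

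**The concern.** Section 4 sets out to evaluate the device. A difference between the two readings, or the lack of one, can be credited to the device only if nothing else differs systematically between the two signal paths. Step IV supplies that premise by asserting a common position. Sections 8-3 and 8-4 contradict it, and the primary endpoint as worded compares locations and does not mention the device.

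Section 8-3 then treats the within-person design as a reason to have no allocation. A patient who serves as their own control cancels what is common to both readings, such as age, drug levels and depth of anaesthesia. A difference tied to where a set sits, or to which input it feeds, is not common to both and stays in the paired difference.

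The protocol itself treats position as important: its background section says that BIS becomes less reliable and signal quality falls when the sensor is moved away from its proper site.

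Two errors are possible. A device that reads perfectly could appear to differ from the conventional sensor, or a real device bias could be cancelled by an opposite offset and reported as agreement. The second would favour the conclusion that section 8-5 sets out to prove.

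**Working it through.** **Plan's own figure.** The only number is 20 patients. It comes without alpha, power, SD, effect size or margin, so there is nothing to reproduce. The question here is whether the device effect can be identified, and that does not depend on the sample size.

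**Model.** For patient i let the paired difference (needle minus conventional) be

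D_i = δ + s_i·b + e_i,

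where δ is the device effect, b is a constant position or input offset, and s_i is +1 or −1 according to which position or input carries the needle set. The model assumes that the offset is the same in all patients and reverses sign when the sets are swapped.

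**What can be estimated with n = 20** (design matrix with columns 1 and s):

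- *Same placement in all 20.* The two columns are identical and the rank is 1. Only δ + b can be estimated, so the whole offset enters the device estimate.
- *Unplanned 15/5 split.* The mean of s is (15 − 5)/20 = 0.5, so half of b enters the unadjusted mean. If placement was recorded and is modelled, δ can be estimated with variance factor 1/(1 − 0.5²) = 1.33.
- *Balanced 10/10.* The mean of s is 0 and the rank is 2. The offset cancels from the mean, and the variance factor is 1.00 with placement in the model.

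**Size if placement is fixed.** Set δ = 0 and use a two-sided 5% paired t-test with 19 degrees of freedom. The noncentrality is b/(SD/√20). For b = 3 and SD = 5 it is 3/(5/4.472) = 3/1.118 = 2.68, which gives a rejection probability of 0.721. Both b and the SD of the differences are assumptions, in BIS points; the protocol gives neither.

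| Assumed offset b | SD 3 | SD 5 | SD 8 |
|---|---|---|---|
| 0 | 0.050 | 0.050 | 0.050 |
| 1 | 0.294 | 0.136 | 0.083 |
| 2 | 0.807 | 0.397 | 0.186 |
| 3 | 0.989 | 0.721 | 0.357 |
| 5 | 1.000 | 0.989 | 0.755 |

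**Masking.** With δ = +3 and b = −3 the expected difference is 0, and the test fails to reject 95% of the time. Exact cancellation is an extreme case, but partial cancellation works in the same direction.

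**Price of balancing.** At an assumed SD of 5, the 95% confidence half-width is 2.34 points for a fixed placement (19 degrees of freedom) and 2.35 points for 10/10 with placement in the model (18 degrees of freedom).

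**The case against.** A reader might infer that device and location are fully confounded, that the inconsistent wording causes this, and that no analysis could repair it. The document does not support any of these.

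- *Full confounding* requires the needle set to have the same position and input in every patient. The protocol does not say so. Within one patient the two effects are inseparable; across patients the protocol is silent.
- *The wording* does not create confounding. It leaves its extent unknown.
- *Repair* is possible if placement varies and is recorded, as the 15/5 case shows. It is not possible if placement is fixed, or if it varies and is not recorded.

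There is also a fair case that the sets are meant to be co-located. Steps I and IV are the instructions that staff would follow, and the phrases in 8-3 and 8-4 may loosely mean two signal sources. If so, the location part largely disappears and only the input part remains. The documents do not rule out near-overlap of 13 mm needles and an adhesive sensor. The input part is itself an inference from the two-area display and the four-channel monitor; no section says that the inputs differ.

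Finally, the rejection rates describe a single paired t-test, not the repeated ANOVA with sequential comparisons in section 8-5, and they move strongly with the assumed offset.

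All of this limits how strongly the point can be put. It does not rescue the inference in 8-3, and it does not settle which placement description governs.

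**Conclusion.** The point holds in conditional form. The protocol gives two descriptions of placement that cannot both be right, and it rejects allocation for a reason that does not justify rejecting it. A device difference therefore cannot be reliably separated from a position or input offset. The confounding is uncontrolled, and it is complete only under a fixed placement.

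The identifiability result needs no numerical assumption beyond a constant offset. The size does: for fixed placement and offsets of 2 to 3 points, the false-difference rate runs from 0.19 to 0.99 over SDs of 3 to 8, against a nominal 0.05. With no offset there is no harm. The protocol gives no information on which of these applies.

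This is a design matter, settled when the electrodes are attached, so a later analysis plan cannot be relied on to deal with it. That section 8-5 names no placement term is not a fault on its own, since such detail may sit in an analysis plan.

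**What to change.** 1. Reconcile section 8-1 (steps I and IV), section 8-3 and section 8-4 so that they describe one and the same placement, and word the primary endpoint as a comparison of the needle interface with the conventional sensor.
2. Replace section 8-3 with a balanced assignment (10/10), randomised or alternating, of whatever the layout allows to be swapped: the monitor input and, if the sets are not truly co-located, the side or relative position.
3. Record the assignment for each patient and include it as a term in the analysis.

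The cost is a 20-line list and one degree of freedom, which widens the 95% interval from ±2.34 to ±2.35 points at an assumed SD of 5. No extra patients are needed.

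One thing must be confirmed first: the document does not show whether sides or inputs can be exchanged with the listed bilateral sensor and the four-lead needle interface. If they cannot, the placement and input used should still be recorded for each patient, and the conclusion limited to the combined effect of device plus position and input.

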#### 4. Aim of the study

To evaluate the clinical performance and safety of a newly developed BIS monitoring converting device using already existing needle electrodes in patients undergoing perioperative EEG monitoring as a subject.

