## 9. Discontinuation criteria

At the following conditions, the study will be discontinued.

- Consent is withdrawn by patients
- Study physicians decide it inappropriate to continue the study

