## **13. Consent of patients (informed consent)**

Before perioperative period, consent will be obtained from the participants after explaining about the study. A withdrawal form will be handed out, and if the patient withdraws the consent by giving the withdrawal form or explaining verbally before the anesthesia introduction, the patient will be excluded from the study.

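### Loss of the needle channel is not counted as non-performance, and a classical repeated ANOVA could also shed patients with missing pairs

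*Protocol*

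**What the plan says.** Section 4 of the protocol gives the aim as "To evaluate the clinical performance and safety of a newly developed BIS monitoring converting device". Section 8-4 names one endpoint that bears on performance: "Primary endpoints : BIS-related values from two different measurement locations". The secondary endpoint is complications. Section 8-3 explains that there is no allocation: "This study acquires and compares information from two sensor locations in a single person". The analysis in section 8-5 reads: "By repeated ANOVA (post hoc test) and sequential two-group comparisons of BIS-related values, it will be proven that the observed values are the same". Section 6-1 sets the size: "The target number of cases: 20 patients".

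Two other places bear on absent readings. Step IV of section 8-1 says that "values calculated using EEG processing, such as SQL, SEF, Beta-ratio, and resting ratio, will be compared and recorded if there is any discrepancy". Section 9 allows a stop when "Study physicians decide it inappropriate to continue the study".

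The protocol has no endpoint for whether the needle channel delivers a reading. It does not fix the number of time points, and it does not say what happens to a patient with an incomplete series.

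**The concern.** A difference between pick-ups exists only at moments when both channels return a value. A device that goes blank for part of an operation, or for all of it, produces no difference in that period and so cannot score worse on the primary endpoint. For a study of clinical performance this is a gap in the endpoint definition, and endpoint definitions belong in the protocol.

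The named method can add to the problem. Classical repeated-measures ANOVA needs every cell, so one missing pair removes the whole patient from that analysis. The stated goal is to show sameness using tests of difference. Both possible consequences therefore point the same way: losing poor-signal patients shrinks the apparent difference, and losing any patients lowers the power to detect one.

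**Working it through.** The only input from the protocol is n = 20 (section 6-1), given without a derivation, so there is no sample-size calculation to reproduce. Failure rate, number of time points, SD and effect size are not given. Every rate below is an assumption.

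**1. Patients left in a classical repeated ANOVA.** If each pair is missing independently with probability q at each of T time points, the expected number of complete patients is 20 × (1 − q)^T.

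| T | q = 1% | q = 2% | q = 5% |
|---|---|---|---|
| 5 | 19.0 | 18.1 | 15.5 |
| 10 | 18.1 | 16.3 | 12.0 |
| 20 | 16.4 | 13.4 | 7.2 |

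For example, 20 × 0.95^10 = 20 × 0.599 = 12.0.

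**2. Effect on power.** For a two-sided 5% paired t-test and a standardized difference of 0.5 (noncentral t), power is 56.5% at n = 20, 46.5% at n = 16 and 35.3% at n = 12. Fewer complete patients make a finding of no difference more likely, whatever the reason for the loss.

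**3. Effect on the estimated difference.** Simulation of 20 patients with 10 time points. On average 20% of patients have poor agreement (mean difference −8, SD 12 BIS points); the rest have mean 0, SD 4.

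| Missingness per time point | Data used | Complete patients | Mean difference | SD |
|---|---|---|---|---|
| None | full data | 20 | −1.58 | 7.0 |
| Linked: 15% in poor, 0.5% in others | available pairs | – | −1.40 | 6.8 |
| Linked: 15% in poor, 0.5% in others | complete cases | 16.0 | −0.38 | 4.9 |
| Unrelated: 3.4% in all | complete cases | 14.2 | −1.59 | 7.0 |

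(In the unrelated run the full-data values were −1.59 and 7.1.)

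The linked result can be checked by hand. The complete fraction is 0.2 × 0.85^10 + 0.8 × 0.995^10 = 0.039 + 0.761 = 0.800, or 16.0 of 20 patients. Poor-agreement patients make up 0.039/0.800 = 4.9% of these, so the expected mean is −8 × 0.049 = −0.39. For available pairs the poor share is 0.17/(0.17 + 0.796) = 17.6%, which gives −1.41.

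So the bias depends on whether loss is linked to disagreement. Under linkage, using every observed pair removes most of it. With unrelated loss there is no bias, only fewer patients.

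**4. What no analysis of pairs can show.** A patient whose needle channel never returns a value contributes no pair under any of these methods. Only an endpoint that counts availability registers that patient.

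**The case against.** The strongest objection is that much of this belongs in a statistical analysis plan. The protocol never says that incomplete patients are dropped; that is inferred from the name of the method. Handling of missing data is commonly left to an analysis plan, which may exist and is not shown. The sentence in section 8-5 also names sequential two-group comparisons, which can use every pair present at a given time. All of this stands. It limits the ANOVA part of the point to a conditional statement, and a claim that the plan as a whole discards valid pairs would be wrong. It does not answer the endpoint gap, because the two-group comparisons are also silent when the needle channel is.

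A second objection is that step IV of section 8-1 already records discrepancies, including in what appears to be the signal quality index. A lost channel could be noted there, so failure need not go wholly unrecorded. But a note is not a counted endpoint.

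A reader might go further and infer that agreement is bound to be overstated. The documents do not support this, because it requires loss to track disagreement. Section 3 links lower signal quality to poorer BIS reliability, but for a conventional sensor moved from its usual position. That makes the link plausible for the needle channel without establishing it.

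A reader might also infer bias from early stops or from operations of different length. Section 9 does not mention the device and does not say that data up to a stop are discarded. Operation length has no stated tie to device performance, and no clock-time grid is fixed. For patients who withdraw before induction, section 13 says that "the patient will be excluded from the study"; no intraoperative comparison data exist by then, so this cannot select on agreement.

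**Conclusion.** The point holds in a limited form. The protocol sets out to assess clinical performance but defines no endpoint in which loss of the needle or interface channel counts against the device. That follows from sections 4 and 8-4 as written.

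The rest is conditional. If the repeated ANOVA is run classically, patients with any missing pair leave that analysis. If channel loss also tracks poor agreement, agreement may be overstated. If it does not, the cost is precision, which still favours a conclusion of no difference.

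The size cannot be established, because no failure rate is given. The figures of about 18, 16 or 12 complete patients out of 20 assume 10 time points and independent loss of 1%, 2% or 5% of pairs. The simulated shift from −1.58 to −0.38 rests wholly on the assumed link and shows direction only. The change is worth making because it is cheap and affects what the study can conclude about performance.

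**What to change.** In section 8-5, replace the repeated ANOVA with a linear mixed model of the within-patient difference (needle minus commercial sensor). Give it a random patient effect and use anaesthetic phase (induction, maintenance, emergence) as the time factor; section 8-1 already follows the patient through these phases. Use every observed pair, including those from interrupted or stopped cases, unless the patient has withdrawn consent to use of the data.

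In section 8-4, add a co-reported performance measure: for each pick-up, the share of monitored time with a displayed BIS value. Take all patients in whom needles were placed as the denominator, and count complete loss of the needle channel as a performance failure. The mixed model cannot stand in for this measure, because it sees nothing of a patient without pairs.

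The cost is rewording two sections and slightly more analysis work. No patients or procedures are added, since section 8-1 says the monitoring system can display values from two areas. The downside is a performance figure that may look less favourable.

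### The primary endpoint is an open set of BIS-related values with no deciding parameter or time window, and the planned comparisons are not said to be paired

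*Protocol*

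**What the plan says.** Section 8-3 describes a within-person design: "This study acquires and compares information from two sensor locations in a single person". Section 8-4 states "Primary endpoints : BIS-related values from two different measurement locations" and names no parameter, summary or time window. The family is given only by example in section 8-1, step IV: "values calculated using EEG processing, such as SQL, SEF, Beta-ratio, and resting ratio". These four come in addition to the BIS value itself, and the list is left open. SQL is presumably the signal quality index, SQI, of section 3.

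Section 8-5 gives the method, "By repeated ANOVA (post hoc test) and sequential two-group comparisons of BIS-related values", and the purpose, "it will be proven that the observed values are the same". It does not state whether the two-group comparisons are paired, which post hoc test is meant, or which comparison settles the question. Section 6-1 sets the size: "The target number of cases: 20 patients".

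**The concern.** When several parameters are primary and are compared repeatedly, some are likely to agree and some to differ. The protocol has no rule for reading a mixed result, for example BIS agreeing throughout while SEF differs at some times. The parameters or periods reported as agreeing could then be chosen after the data are seen.

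The label two-group is commonly used for independent samples. If it were applied that way here, variation between patients would stay in the error term. The main advantage of placing both sensors on one person would be lost, and a real bias between them would be harder to see. In a study that intends to conclude sameness, that is the more harmful direction.

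**Working it through.** The protocol states no alpha, power, SD, correlation, acceptable difference or number of time points, so it has no figure of its own to reproduce. What follows is an illustration.

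**Inputs from the protocol:** 20 patients (6-1); both readings from one person (8-3); four derived parameters plus BIS, so about 5 (8-1, step IV).

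**Assumed inputs:** two-sided alpha 0.05 per test; 1, 5 or 10 time points; correlation between the two sensors' readings, ρ, of 0.5 to 0.8; true bias 0.5σ, where σ is the between-patient SD.

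**1. Paired, unadjusted tests with truly identical devices**

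For k independent tests, P(at least one p < 0.05) = 1 − 0.95^k.

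| Tests | Independent | Correlated (simulated, n = 20) |
|---|---|---|
| 5 (one time) | 1 − 0.95^5 = 0.226 | 0.19 (r = 0.5); about 0.14 (r = 0.8) |
| 25 (5 × 5) | 1 − 0.95^25 = 0.723 | 0.60 (0.5/0.5) |
| 50 (5 × 10) | 1 − 0.95^50 = 0.923 | 0.83 (0.5/0.5); 0.70 (0.5/0.8); 0.55 (0.8/0.8); 0.49 (0.7/0.9) |

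Pairs in brackets are the correlation between parameters and the lag-one correlation over time. The simulations used paired t-tests and 10,000 replicates.

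**2. Paired against unpaired tests, one comparison, n = 20**

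- SD of the paired difference: σ√(2(1 − ρ)). At ρ = 0.5 this is 1.00σ; at ρ = 0.8 it is 0.632σ.
- True standard error of the mean difference: σ√(2(1 − ρ)/20), which is 0.224σ at ρ = 0.5 and 0.141σ at ρ = 0.8.
- Standard error that an unpaired test uses: about σ√(2/20) = 0.316σ whatever ρ is. It is too large by a factor 1/√(1 − ρ): 1.41 at ρ = 0.5 and 2.24 at ρ = 0.8.
- Paired power for a bias of 0.5σ, from the noncentral t with 19 degrees of freedom and noncentrality 0.5/√(2(1 − ρ)) × √20. At ρ = 0.5 the noncentrality is 2.236 and power is 0.56. At ρ = 0.8 they are 3.536 and 0.92.
- Unpaired power (simulated, 200,000 replicates): 0.28 at ρ = 0.5 and 0.22 at ρ = 0.8.
- Unpaired false-difference rate per test (simulated): about 0.007 at ρ = 0.5 and about 0.0002 at ρ = 0.8, against the nominal 0.05.

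The two parts describe alternative readings of section 8-5. The inflation in part 1 requires paired tests. The loss of detection in part 2 requires unpaired ones.

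**The case against.** A reader might infer that the plan ignores the pairing. The text does not show this. Section 8-5 never says unpaired, a repeated ANOVA is ordinarily a within-subject analysis, and section 8-3 recognises the within-person design. A two-group comparison can also mean a paired test of two sets of readings. What stands is that the plan does not say the comparisons are paired and uses a label that invites the other reading.

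A reader might also infer that the error rates are wrong in both directions at once. They cannot be, at the sizes shown, because each effect belongs to a different reading.

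Nor can it be said that multiplicity is uncontrolled. The post hoc test may carry an adjustment, and its details may properly sit in a statistical analysis plan that is not shown. It would not evidently cover the separate sequential comparisons or the several parameters, but that gap alone would be a weak point. Sequential is also undefined, so testing at every time point is an inference.

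Finally, extra false differences work against a claim of sameness, and a multiplicity correction on its own would make that claim easier to reach. This is correct, and it is why the fix does not rest on such a correction.

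None of this answers the endpoint problem. Naming the primary endpoint is a matter for the protocol, and section 8-4 does so with an open list.

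**Conclusion.** The point holds in a limited form. Sections 8-4 and 8-5 together leave no single comparison that decides the study, and the method as written has no interpretable error rate. Depending on how the comparisons are run, either chance differences between identical devices become common, or a real bias is more easily missed.

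The sizes rest wholly on assumed inputs and vary widely with them, so they show what could happen and do not estimate this trial's error rates. Even the statement that identical devices would usually show a difference fails in the most strongly correlated 50-test case, at 49%.

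A related limit bears on the repair: a mean difference near zero does not show that the values are the same, because individual readings can still disagree widely. An agreement criterion is needed as well as a single primary. The change is worth making, but it is not a fatal fault in the design.

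**What to change.** In section 8-4, name one primary endpoint: the within-patient difference in BIS, needle electrodes minus standard sensor, over a stated period. Make SQI, SEF, beta ratio and the resting ratio secondary and descriptive.

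In section 8-5, replace the sequential two-group tests with one analysis of the paired differences that allows for repeated measurements within a patient, for example a mixed model with a patient random effect. Report the mean difference with its confidence interval and the limits of agreement. Judge them against an acceptable difference that the sponsor chooses and writes down in advance. Show differences at individual time points as estimates with confidence intervals, without tests.

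The cost is rewording two sections and slightly more analysis work. Patients, devices and recording need not change. The downside is that the other parameters lose primary status.

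### In its classical form, the repeated ANOVA named in 8-5 has an error term that suits neither the device-by-time test nor pooled-error post hoc tests if needle-minus-sensor differences are serially correlated or vary in spread by phase

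*Protocol*

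**What the plan says.** The whole analysis plan in the protocol is the one sentence in section 8-5: "By repeated ANOVA (post hoc test) and sequential two-group comparisons of BIS-related values, it will be proven that the observed values are the same". It sets the two methods side by side and ranks neither.

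The data come from a within-patient comparison. Section 8-3 says "This study acquires and compares information from two sensor locations in a single person", and section 8-4 gives "Primary endpoints : BIS-related values from two different measurement locations". Section 8-1 takes the readings through different phases. Both pick-ups are attached before induction (step I) and induction follows (step II). For step III it says "Normal anesthesia management will be done". After surgery "it will be recorded if there is any discrepancy and if so in which degree in increasing BIS values due to emergence" (step V). Section 6-1 sets the size: "The target number of cases: 20 patients".

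The protocol gives no number or timing of readings, no SD, no correlation, no significance level, no sphericity correction and no error term for the post hoc tests.

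**The concern.** With two pick-ups per patient, everything the ANOVA says about the device rests on the needle-minus-sensor difference at each time. The classical device-by-time test is valid only if those differences meet sphericity: the difference between any two time points must have the same variance. Two ordinary features of such a record would break this. Device-specific error may persist from one reading to the next, so that neighbouring differences are more alike than distant ones. The differences may also be more variable while BIS is moving than in steady maintenance.

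The two features do different harm. Either one inflates the device-by-time test. Only unequal spread makes a pooled post hoc error too small at induction and emergence and too large in maintenance. Steps IV and V ask whether the pick-ups differ, by how much, and specifically at emergence, so the phase-specific comparisons are central to the study. At stake are false signals of disagreement at the ends of the case and a real maintenance offset that goes unnoticed.

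**Working it through.** The protocol states no error rate or power, so there is no figure of its own to reproduce.

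**Inputs from the protocol.** n = 20 patients (6-1); two pick-ups per patient, so the device factor has 1 df (8-3); phases from induction to emergence (8-1).

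**Assumptions, not in the protocol.** T = 5, 10 or 20 readings; AR(1) lag correlation of the differences from 0 to 0.95; maintenance SD of 3 BIS points; SD in the first and last fifth of the record equal to k = 1, 2 or 3 times that; two-sided 5% tests. Each scenario was simulated 6,000 times.

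**1. Device-by-time test, identical pick-ups.** The uncorrected F test uses T−1 and (n−1)(T−1) df. Without sphericity both are effectively multiplied by ε < 1. Example: T = 20, lag correlation 0.8, equal SDs.
- Nominal df are 19 and 19 × 19 = 361, with critical value 1.615.
- ε = 0.296, so the effective df are 0.296 × 19 ≈ 5.6 and 0.296 × 361 ≈ 107.
- P(F with 5.6 and 107 df > 1.615) ≈ 0.15. The simulation gave 13.6%.

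Simulated ranges:

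| Cause | Uncorrected |
|---|---|
| Lag correlation 0.5–0.95, equal SDs | 6.5–17.7% |
| Unequal SDs, no lag correlation | 7.5–10.1% |
| Both | 8.0–19.3% |

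Across these scenarios the Greenhouse-Geisser correction gives 1.9–5.4%.

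**2. Device main effect (1 df).** It rejects in 4.5–5.6% of runs in every scenario. There is no inflation.

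**3. Post hoc tests with a pooled error.** Two fifths of the readings have k times the SD, so the pooled variance is (3 + 2k²)/5 times the maintenance variance.

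| | k = 2 | k = 3 |
|---|---|---|
| Variance ratio | (3 + 8)/5 = 2.2 | (3 + 18)/5 = 4.2 |
| Pooled SD = 3√ratio | 4.45 | 6.15 |
| Pooled SE = SD/√20 | 0.995 | 1.375 |
| Rejection limit = 1.96 × SE | 1.95 | 2.69 |
| True SE at the ends = 3k/√20 | 1.342 | 2.012 |
| True SE in maintenance = 3/√20 | 0.671 | 0.671 |
| False positives at ends: 2[1 − Φ(limit/true SE)] | 14.6% | 18.1% |
| False positives in maintenance | 0.4% | <0.1% |
| Power, 2-point maintenance gap: Φ((2 − limit)/0.671) | 53% | 15% |

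The simulation, which also varies T and the lag correlation, agrees: 14–20% at the ends and 0–0.7% in maintenance. Power, simulated for T = 5 and 10 with lag correlation 0.5 and 0.8, is 52–53% (k = 2) and 16–17% (k = 3).

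**4. Each time point with its own paired error.** The per-test false-positive rate is about 4–6% in every phase. For the 2-point maintenance gap the noncentrality is 2/0.671 = 2.98 on 19 df, which gives 81% power. The simulation gave 79–82%.

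**5. Which feature causes which fault.** With equal SDs, pooled-error post hoc tests stay at 4.5–6.0% at any lag correlation, and power for the maintenance gap is 83–84%. If the interaction residual is used as the error instead, lag correlation with equal SDs gives about 6–55% in all phases. Maintenance is then over-called, not missed.

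**The case against.** The strongest reply is that 8-5 does not commit to the version criticised. It states neither an uncorrected F test nor a pooled post hoc error, and repeated ANOVA includes the Greenhouse-Geisser form. Covariance structure and correction are commonly left to the SAP, which is not shown. This stands as a limit: the fault is conditional on the classical form being run, and the absence of the detail is not itself the point. It does not remove the point, because the protocol names this method without qualification for phase-crossing data, and a simpler one answers its question without relying on sphericity.

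Two stronger readings are tempting and unsupported. A reader might infer that identical pick-ups will be called different too often by the ANOVA as a whole. They will not: the direct needle-versus-sensor main effect keeps its level. A reader might also infer that serial correlation hides maintenance gaps. It does not: that needs unequal spread together with a pooled error.

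Three further replies are fair. The sequential comparisons in the same sentence escape the fault if they are paired with their own error. The covariance that matters is that of the differences, since the depth-of-anesthesia trend shared by both pick-ups cancels, and the protocol says nothing about what remains. Excess device-by-time rejections would also work against the protocol's intended conclusion, not in its favour.

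**Conclusion.** The point holds in conditional form. If the repeated ANOVA in 8-5 is run uncorrected, and the paired differences are serially correlated or uneven in spread, the device-by-time test runs at about 6.5–19% instead of 5%. If spread is 2 to 3 times larger at the ends and the post hoc error is pooled, agreement is wrongly rejected there in about 14–20% of tests. Power for a 2-point maintenance gap falls from about 80% to 52–53% or 16–17%.

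The direction follows from the method. The sizes rest on the assumed correlations, SDs and numbers of readings, since the protocol gives none, and milder departures would give smaller effects. This is separate from, and smaller than, the fault of using difference tests without a margin to prove sameness. Correcting the error structure leaves that one untouched.

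**What to change.** In 8-5, replace the repeated ANOVA with post hoc test by an analysis of the paired needle-minus-sensor difference. For each patient, take one mean difference per period (induction, maintenance, emergence). For each period, report the mean of the 20 patient values with its own standard error and 95% CI. Each interval rests on independent patients and needs no assumption about correlation or equal spread over time. It also gives the size of the discrepancy that steps IV and V ask for.

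If ANOVA is kept as support, state the Greenhouse-Geisser correction and period-specific error for the post hoc contrasts.

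The cost is wording, with no extra patients or data. Where spread is larger, intervals widen: for a single emergence reading under the assumptions above, the standard error is 1.34 instead of the pooled 0.995 (k = 2), or 2.01 instead of 1.375 (k = 3). The wider figure is the honest one. The change does not deal with multiple testing across time points or measures, or with the lack of an agreement margin; those need their own wording.
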